## Abstract

**Background:**

Physical, emotional, and social changes, including exposure to poverty, abuse, or violence, increases youth vulnerability to mental illness. These factors interfere with development, limit opportunities, and hamper achievement of a fulfilling life as adults. Addressing these issues can lead to improved outcomes at the population level and better cost-effectiveness for health services. Cash transfer programs have been a promising way to address social drivers for poor mental health. However, it is still unclear which pathways and mechanisms explain the association between socioeconomic support and lower mental illness among youth. Therefore, we will evaluate the effect of social drivers on youth mental health-related hospitalizations and suicide, test mechanisms and pathways of a countrywide socioeconomic intervention, and examine the timing of the intervention during the life course.

**Methods:**

We will combine individual-level data from youth national hospitalization, mental health disorders and attempted suicide, suicide registries and notifications of violence, with large-scale databases, including “The 100 Million Brazilian Cohort”, over an 18-year period (2001–2018). Several approaches will be used for the retrospective quasi-experimental impact evaluations, such as Regression Discontinuity Designs, Propensity Score Matching and difference-in-differences, combined with multivariable regressions for cohort analyses. We will run multivariate regressions based on hierarchical analysis approach to evaluate the association between important social drivers (mental health care, demographic and economic aspects) on mental health-related hospitalizations and suicide among youth. Furthermore, we will perform microsimulations to generate projections regarding how mental health-related hospitalizations and suicide trends will be in the future based on the current state, and how BFP implementation scenarios will affect these trends.

**Discussion:**

The results of this project will be of vital importance to guide policies and programs to improve mental health and reduce mental health-related hospitalizations and suicide in youth. It will provide information to improve the effectiveness of these programs worldwide. If cash transfers can decrease mental health problems among youth and reduce suicide.

## Background

Mental disorders are both common in young people and persistent. Previous study estimates that the global prevalence of mental illness among children and adolescents ranges between 13–20% [1], and nearly 90% of children and youth under the age of 24 years live in low- and middle-income countries (LMICs), where they constitute up to 50% of the population [2] It is estimated that at least half, and up to 75%, of all mental health problems across the life course, emerge before the age of 24 [3]. Addressing the drivers of mental disorders during this developmental phase of the life course offers a critically important opportunity to reduce the global burden of mental disorders.

A range of social adversities and deprivations are drivers of mental illness which affect children and adolescents. Youth in low middle income countries (LMICs) are particularly vulnerable due to the higher prevalence of adversities, for example, poverty, and relatively fewer available social protections in place. There is increasing recognition of the relevance of mental health to global development strategies, in particular to the achievement of the Sustainable Development Goals (SDGs), including improving youth mental health and eradicating poverty (https://sdgs.un.org/goals). Since mental health problems affect a large proportion of youth, have profound effects on a range of social outcomes such as education and employment, and can persist into adulthood, addressing mental health problems in youth is a priority for the global health agenda and for realizing the SDGs. However, there is evidence that access to mental health services in Brazil is limited, as only 19% of children with mental illness from schools in São Paulo and Porto Alegre were reported to have had prior treatment [4].

A primary strategy for achieving the SDGs is to reduce the incidence of mental disorders, for example by targeting social determinants. Additionally, there is an ethical responsibility to address the most vulnerable young people so that existing mental health disparities can be reduced [5].

Preventing mental illness earlier during development could decrease subsequent mental health-related hospitalizations and suicide attempts. However, prevention poses a tough challenge, as these outcomes are usually the final stage of a series of small breakdowns that happen at several levels in the life course. Considering the multi-causality of the phenomenon, it is important to investigate several social drivers, risks, and protective factors at the individual and contextual level. Poverty, gender and racial inequality are associated with increased mental illness [6] and suicide [7, 8]. This might be explained by increased stress, family difficulties, alcoholism, impulsivity, violence and parental mental illnesses among the poor [3, 9–11]. However, those mechanisms are yet to be fully understood and tested, especially among youth in a LMIC setting.

Brazil has one of the largest mental health-related hospitalizations among youth, and suicide is the third most common reason for death due to external causes, and alarmingly both have increased over the last 13 years. The World Health Organisation (WHO) recommends that suicide prevention should be prioritized on the global public health agenda [12]. However, it remains unclear what interventions are best suited for targeting youth at a population level and what preventive interventions delivered earlier in life have a long-term effect on preventing mental health-related hospitalizations and suicide.

The Brazilian government introduced the Bolsa Familia Programme (BFP) in 2003 [13] to promote social inclusion and strengthen human capital among the poorest. Poverty alleviation programs could influence mental illness by diverse pathways [3, 5, 9] through decreasing income inequalities or by reducing socioeconomic hardship through increased family income, which might result in stress reduction, less family disruption, or decreased alcohol consumption [14]. Therefore, we might expect government poverty alleviation programs such as BFP to have an impact. However, whether this Brazilian government program has impacted, and knowledge of the pathways and mechanism of its impact, on youth mental illness and suicide remains unknown.

Our data of over half of the Brazilian population will help understand both (observationally) the association of multiple factors on both mental illness and suicide, and the impact of interventions targeting some of these factors. Within each broad analysis, we will explore pathways, mechanisms and interactions/moderators. This is especially important in LMICs, such as Brazil, where implementing preventative measures may be more challenging as a result of cultural and socioeconomic factors, limited resources, as also in large continental countries because of size and distribution of the population [15]. This study’s aims are as follows:
To use large national datasets to evaluate the effect of a broad range of social drivers and of a social-economic intervention on youth mental health,To test four mechanisms and pathways (reducing parental mental illness; increasing school retention; reducing exposure to violence; decreasing impulsivity) of the social-economic intervention on reducing mental illness among youth,To evaluate whether equity is a moderator of the effectiveness of the cash transfer program, e.g., whether the Brazilian cash transfer program improves the lives of the most vulnerable subgroups (with lower income, black population, and women) compared to less vulnerable groups, thereby reducing mental health disparities, andInvestigate early life exposures, intergenerational aspects, and to forecast the impact of socioeconomic changes and cash transfers mitigation effects in Brazil until 2030 using microsimulation models, also modelling the impact of the current COVID-19 related economic recession.

## Study innovation

The Brazilian Cash Transfer Program, “Bolsa Família Program” (BFP), is one of the largest conditional cash transfer programs worldwide, which appears to have had an important public health impact. Studies indicate that BFP has promoted social inclusion and strengthened human capital among the poorest, reducing poverty and inequalities, besides increasing school attendance among youth and reduced violence, factors that are associated with mental health [5, 7, 10, 16]. A recent study found that municipalities with higher coverage of the BFP had lower suicide, indicating that this program may have some reduction effect [7]. However, understanding the impact of this program at the individual and contextual level, analyzing by areas and municipalities, and investigating pathways and mechanisms for preventing mental health-related outcomes remains unexplored. Evaluating the impact of these changes is of great interest for health systems in LMICs such as Brazil, where dramatic socioeconomic changes have taken place in a short time. If Brazilian programs are associated with lower hospitalization from mental illness and suicide, there may be ways to support prevention through increased program coverage and integration with the current mental health strategy.

*First*, this study provides a unique opportunity to use the largest existing longitudinal dataset (The 100 Million Brazilian Cohort) in any LMIC of linked socioeconomic and health individual-level data to assess the effects of socioeconomic conditions and BFP on mental illness and suicide among young people.

*Second*, the longitudinal aspect of the cohort, with a long follow-up period of 18 years of socioeconomic and health data, will allow us to explore and assess in-depth dynamics, lagged and long-term effects of changes in living conditions, parents’ mental illness and in exposures to BFP. The long-term impact of BFP on a diverse population once such a program has been scaled up and sustained for over a decade is completely unknown.

*Third*, with this project, we will be able to identify risk factors for mental health-related hospitalizations and suicide (such as demographic factors, economic factors, parents’ underlying mental illness and substance use disorders) and investigate pathways and mechanisms using a linkage of massive datasets covering half of the country for sociodemographic information and the full country for hospitalization and mortality information.

*Fourth*, the uniquely large number of individuals of our dataset provides sufficient statistical power to assess the effects and test mechanisms of BFP on a high number of subpopulations, in terms of demographic, geographic, social, and economic conditions, thereby taking advantage of Brazil’s extreme social inequalities. To date, knowledge about the potential of Cash Transfer Programs (CCTs) on mental illness and suicide has been limited to small trials where, in general, the CCT program was not part of a national poverty alleviation strategy, and evaluations have been focused on poor populations of a few lower-income countries. This study provides the exceptional occasion to assess potential effect modification disparities, evaluating whether the Brazilian cash transfer program improved the lives of most vulnerable subgroups (with lower income, black population, and women) compared to less vulnerable groups, therefore, reducing inequalities.

*Fifth*, this study contributes to translational science with the systematic integration of the large dataset and results from retrospective impact evaluations with prospective mathematical models, developing more reliable forecast scenarios than models which use parameters from other studies or populations. The 18 year-100 million individual retrospective cohort will be used to generate projections, using microsimulation models, of an integrated synthetic cohort up to 2030, maintaining the correlation structure between variables and area/individual-specific trends in all demographic and socioeconomic variables. In creating these forecast cohorts, several alternative scenarios–including maintenance of the current poverty and inequality increase vs their gradual decrease—will be simulated, and resulting effects on mental health-related hospitalizations and suicide (as well as the policy response to it) will be evaluated.

This project provides an innovative approach to assess the effects of a large and successfully scaled program on youth mental illness and suicide. Use of a longitudinal big dataset and a pioneer integration between retrospective and forecasting evaluations, together with innovative hybrid microsimulation models, will advance our understanding of mental illness, suicide, and control measures among youth in one of the biggest countries in the world. The implications are vast, as it will help answer questions about mechanisms through which socioeconomic programs can prevent mental illness in early life. These findings will be important to other LMICs struggling to address the mental health burden and to other countries, that also faces high-income inequality, high violence rates and its continental size, which brings challenges to implementing governmental programs.

## Materials and methods

### Conceptual framework

There is a strong association between poverty and poor mental health in young people [17, 18]. Psychiatric disorders in youth are often associated with social problems such as school failure or delinquency, which increase the risk of poverty and other adverse outcomes into adulthood [3, 5]. Furthermore, mental health support is inequitably distributed, so that people living in poverty and those facing other vulnerabilities are at higher risk [5]. Therefore, youth living in LMICs have increased vulnerability to mental illness and associated high mortality rates due to their social and environmental situations [11, 19].

Economic hardship can affect mental health, increase stress, and decrease self-esteem [20]. Economic stressors have been estimated to account for 24% of suicide occurrence [21]. Income inequality is associated with increased suicide rates for both men and women, mechanisms by which this association exists include limited access to resources and increased sense of injustice for not achieving as much economic success as other people [21]. Some studies indicate that poverty is more frustrating in more unequal communities, possibly because individuals become frustrated when comparing themselves to others [22]. In Brazil, income inequality has been associated with higher suicide rates [8] Poverty can increase predisposition to mental illness such as alcohol abuse/dependence and depression in families [22]. It has been shown that cash transfer programs can improve general mental health [23] and increase hope and optimism [24]. It can also reduce factors that are associated with suicide, such as exposure to violence and impulsivity. Factors that can be tested in the current project by accessing notifications and hospitalizations related to those causes.

Several drivers and mechanisms have been hypothesized to underlie the process of the association between cash transfer and better mental health outcomes, and there is also a bidirectional and intergenerational component. Haushofer and Shapiro (2016) have shown that the receipt of a fixed monthly income resulted in a short-term increase in self-reported welfare among beneficiaries in Kenya [25]. A review summarized the causal evidence and mechanisms for the relationship between poverty and common mental illnesses [5]. Poverty can increase exposure to factors that lead to poor mental health, such as economic tension and family violence. Poverty may also be a barrier to accessing goods, resources and services (which can make it impossible to satisfy even basic needs), contributing to the sense of social injustice generated from inequities in access [22]. Therefore, cash transfers could increase the welfare of beneficiaries by providing greater financial stability, as well as improving family members mental health.

We hypothesize that a socioeconomic intervention, Bolsa Família Program (BFP), could be associated with better mental health outcomes among youth, by mitigating some social drivers for poor mental health, such as exposure to violence [14]. Similarly, the possible BFP effect could be mediated by the reduction of important risk factors for mental illness among youth, parents’ mental illness and school dropout because of child labor. All testable variables in our datasets. By decreasing impulsivity, measured by hospitalizations from injuries, BFP could decrease attempted suicides and suicide cases among youth (Fig 1).

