#### Analytic strategy

Aim 1: To use large national datasets to evaluate the effect of a broad range of social drivers and of a social-economic intervention on youth mental health.

In this step we will evaluate: first the effect of the BFP and social drivers such as family income, poverty, early marriage, housing characteristics, family income, parents’ divorce, family composition, and parents’ substance misuse on youth hospitalization from: (A) mood disorders; (B) anxiety; (C) psychosis; (D) prescribed or illicit drug abuse and dependence; (E) alcohol abuse and dependence; (F) alcohol-related liver, problem/chronic liver disease; (G) physical injuries; and (H) attempted suicide and (I) suicide. We will also evaluate if a family history of violence, suicide and psychiatric disorders will be associated with an increased risk of been hospitalized from a mental illness or been a suicide victim among youth. Also, if the BFP reduced the recurrence of mental health-related hospitalizations.

We will run regressions to evaluate the association between important social drivers listed above on mental health-related hospitalizations and suicide among youth in Brazil from 2001 to 2018. Multivariate regression models based on a hierarchical analysis approach will be adjusted for mental health care access, income, location of residence (urban/rural), household living conditions including household density, water supply, sewage and garbage collection, residency type and building material, and stratified by age groups, sex and race. The hierarchical models will be ordered according to the level that they act on the dependent variables (mental health hospitalizations and suicide). It is argued that mental health is conditioned by a series of proximal and intermediate factors, conditioned by socioeconomic situation, among which level of education, marital status, race, home conditions, region, and place of urban/rural residence, all considered social drivers.

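### The Aim 1 social-driver regressions speak of effects but do not handle the youth's own prior illness, so part of a driver estimate may reflect illness that came first

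*Protocol article*

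**What the plan says.** **Direction of the relation.** The Conceptual framework says "Psychiatric disorders in youth are often associated with social problems such as school failure or delinquency, which increase the risk of poverty"; the full clause reads "which increase the risk of poverty and other adverse outcomes into adulthood". The same section adds, about the link between cash transfer and mental health, that "there is also a bidirectional and intergenerational component". The Background says of admissions and suicide attempts that "these outcomes are usually the final stage of a series of small breakdowns that happen at several levels in the life course".

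**Aim 1 (Analytic strategy).** The stated object is "first the effect of the BFP and social drivers such as family income, poverty", followed by further drivers, on youth admission and suicide. The model sentence uses different language: "We will run regressions to evaluate the association between important social drivers listed above on mental health-related hospitalizations and suicide among youth in Brazil". The models are to be "adjusted for mental health care access, income, location of residence (urban/rural), household living conditions" and further household items, stratified by age group, sex and race. The youth's own psychiatric history is not on this list.

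**BFP analysis, same aim.** The propensity-score matching list does include previous psychiatric hospitalization.

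**Aim 4, Step 2.** Admissions and deaths for 2019–2030 are projected from each individual's variables and the effect estimates of the earlier retrospective analyses.

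**The concern.** Admission is a late event. A youth can be ill for a long time before a first admission, and Table 1 describes the youth cohort as aged 5–24 at registration, an age range in which the Background places the onset of much mental illness. If illness, or the family burden that comes with it, lowers the income or schooling recorded at registration, a later admission for that same illness will count as an outcome of low income or poor schooling. Education shows the difficulty most directly. Aim 1 lists it among the factors that condition mental health, while the Conceptual framework links youth disorder to school failure.

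The estimates also have a second use. In Step 2 they become inputs to projections under rising-poverty scenarios. An association that partly runs from illness to poverty would then misstate the admissions and deaths attributed to poverty. With a cohort of this size, even a small spurious ratio would have a narrow interval.

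**Working it through.** **Text check.** There are two covariate lists under Aim 1.

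| Analysis | Prior psychiatric admission of the youth |
|---|---|
| Social-driver regressions | not listed |
| BFP propensity-score match | listed |

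The variable is therefore available and is treated as a confounder for BFP, but it is left out for the drivers. This is a difference between two stated lists, so it is more than a detail left to a fuller plan.

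**Size.** The protocol gives no figure to reproduce, so this is an illustration. Suppose poverty has no true effect (rate ratio 1.00) and half of the youth are in the lower-income group. Let

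- p = share already ill at registration: 13–20%, the global prevalence in the Background;
- a = chance that an ill youth is in the lower-income half: 0.50 (no influence), 0.55 or 0.60 (assumed);
- R = admission rate in ill relative to other youth: 5 or 20 (assumed).

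Share ill in the lower half: q_L = p·a / [p·a + (1−p)·0.5].

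Share ill in the upper half: q_H = p·(1−a) / [p·(1−a) + (1−p)·0.5].

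Apparent rate ratio = [1 + q_L(R−1)] / [1 + q_H(R−1)].

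Worked case, p = 0.13 and a = 0.60:

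- q_L = 0.078/0.513 = 0.152 and q_H = 0.052/0.487 = 0.107.
- R = 5: 1.608/1.427 = 1.127.
- R = 20: 3.889/3.029 = 1.284.

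| a | R = 5 (p = 13%, 20%) | R = 20 (p = 13%, 20%) |
|---|---|---|
| 0.50 | 1.00, 1.00 | 1.00, 1.00 |
| 0.55 | 1.06, 1.07 | 1.13, 1.14 |
| 0.60 | 1.13, 1.15 | 1.28, 1.29 |

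**Sensitivity to the assumptions.** An a of 0.60 is an odds ratio of 0.60/0.40 = 1.5 for lower income given illness. If the odds were doubled instead, the result would be 1.22–1.27 at R = 5 and 1.53–1.55 at R = 20. If only 2% were ill at registration, it would be 1.03–1.11 at an odds ratio of 1.5, and 1.01–1.20 over odds ratios of 1.2 to 2.0.

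**What a lag could do.** If the excess admission rate of ill youth faded to R = 2 after the lag, the ratio at a = 0.60 would fall to 1.152/1.107 = 1.04 (p = 13%) or 1.231/1.167 = 1.05 (p = 20%). The fade is assumed.

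**Limit of prior admission as a marker.** The Background reports that "only 19% of children with mental illness from schools in São Paulo and Porto Alegre were reported to have had prior treatment", which leaves 81% of that sample without prior treatment. The sample comes from schools in two cities and concerns treatment of any kind, but it suggests that prior admission identifies only part of existing illness.

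**The case against.** The strongest reply has four parts.

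1. **The reverse path is stated loosely.** The sentence in the Conceptual framework describes an association, an indirect route through school failure or delinquency, and consequences reaching into adulthood. Aim 1's drivers are largely family income and housing of children and young people. The sentence does not say that a youth's illness lowered the income on the register, and the bidirectional remark concerns cash transfer and mental health. This stands. A reader might infer that part of the driver effect does run backwards; the documents support only that it may.

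2. **The missing lag is silence.** Aim 1 sets no start of time at risk, and Study innovation promises analysis of lagged and long-term effects of living conditions. A reader might infer that the plan chose to count admissions from registration with no lag. The text does not say so, and an article may leave lag length to a fuller plan. The omission from a stated covariate list is a different matter.

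3. **Much of the wording is already associational.** The aims separate observational association from the impact of interventions, and the Aim 1 model sentence says association. That is fair, but Aim 1 also says effect, and Step 2 uses the estimates as effects.

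4. **Registration is not always a response to lost income.** Data and measures says that social workers also visit homes to register eligible people. This weakens the mechanism without removing it.

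A reader might also infer that the same admissions bias the BFP estimates towards harm. The documents do not support this: the match includes income and previous psychiatric hospitalization, and regression discontinuity and difference-in-differences analyses are planned beside it. Nor would it be right to discard any effect confined to the first year, since hardship may have real short-term effects.

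**Conclusion.** The point holds for the Aim 1 social-driver regressions only. Followed as written, the adjustment list leaves the youth's own prior illness unhandled, although the document acknowledges a long course before admission and a two-way element, and uses the needed variable in the adjacent analysis. Part of a driver estimate may therefore reflect illness that preceded the recorded driver.

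The size is unknown. With 13–20% already ill and the assumed 50–60% and 5–20-fold inputs, the spurious ratio lies between 1.00 and about 1.3. It is nil if illness does not affect recorded family circumstances, and larger only under stronger assumptions. The change is worth making because the data are already linked and the estimates go on into the projections.

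**What to change.** For the social-driver regressions in Aim 1:

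- In the first-event analysis, exclude youth with a linked psychiatric admission or self-harm record dated before the driver was recorded. Keep them for the recurrence analysis.
- Add a sensitivity analysis that starts counting outcomes 12 months after registration, and report the driver estimates by time since registration (for example 0–1, 1–3 and over 3 years).
- Use association wording for the drivers throughout.
- In Step 2, run the projections with the lagged estimates as well and show the difference.

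The change needs some plan text and repeat runs on data already linked. Slightly fewer events enter the first-event and lagged analyses. Because the linked records begin in 2001, youth registered early have a short look-back. Long-standing illness that never led to admission is only partly removed, and the report should say so.
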